#### Child post-traumatic cognitions inventory

The Child Posttraumatic Cognitions Inventory (CPTC) [35] is a self-report questionnaire that measures trauma-related cognition in children and adolescents. The questionnaire consists of 25 items that can be answered on a four-point Likert scale (range from 1 (strongly disagree) to 4 (strongly agree). The English version of the CPTCI has been validated for children and adolescents aged 6–18 years. The Dutch CPTCI has good reliability and validity [36], high internal consistency (Cronbach's 0.86–0.93), and good convergent validity.

#### Child behavior checklist

The Dutch parent-report version of the Child Behavior Checklist 6–18 years (CBCL) assesses a wide range of children's emotional and behavioral problems, aiming to identify children at a high risk of psychiatric disorders. The CBCL/6–18 comprises 120 items assessing behavioral and emotional problems. These items are answered on a 3-point Likert-type scale (0 = not true, 1 = somewhat or sometimes true, 2 = very true or often true) by parents. The scores display eight problem scales: withdrawn (1), somatic (2), anxious (3), social (4), thought (5), attention (6), rule-breaking (7), aggressive (8), and other problems. The sum of problem scales 1, 2, and 3 forms the scale ‘internalizing behavior’; 7 and 8 form ‘externalizing behavior.’ All subscales comprise the total problem scale. Some items contribute to more than one problem scale. The CBCL assesses a broad array of potential trauma-related symptoms, including those not captured by a PTSD-specific measure. T-scores are computed from raw scores; higher scores on the syndrome scale indicate greater severity of problems. A T-score of 63 (90th percentile) demarcates the clinical range, indicating that the child requires professional assistance. The CBCL/6–18 has well-established psychometric properties in clinical, non-clinical, and cross-cultural populations [37].

#### Youth outcome questionnaire

To assess the therapy outcome in terms of changes in symptom level, we will use the Dutch translation of the Youth Outcome Questionnaire [38]. The Y-OQ-30 has 30 items and can be completed in 10–15 min on a 5-point Likert scale with a range of 0 (never) to 4 (always). The Y-OQ-30 has six subscales: Somatic complaints, Social Isolation, Aggression, Behaviour problems, Hyperactivity, and Depression/ Anxiety. The Y-OQ-30 is a valid and reliable test for assessing changes [39].

#### Parental stress questionnaire

The OBVL (“Opvoedingsvragenlijst”) is a 34-item parent report questionnaire that measures experienced parental stress [40]. The questions are answered on a 4-point scale (1 = does not apply, 2 = applies a little, 3 = applies fairly, and 4 = applies completely). Scores on the subscale of problems in the parent–child relationship range from 6 to 24, where a score of 14 or higher indicates severe problems, for which treatment is indicated. Scores on ‘parenting problems’ range from 7 to 28, with a score of 18 or higher indicating severe problems [41]. The OBVL demonstrated good reliability and validity.

### Other measurements

#### Children's revised impact of event scale

The Children's Revised Impact of Event Scale (CRIES-13) [42] is a brief self-report questionnaire designed to screen for PTSD in children aged 8 years and older. It consists of 13 questions assessing posttraumatic intrusions, avoidance, and arousal. Children rated the frequency with which they had experienced each item during the past week using a four-point Likert scale (0 = not at all, 1 = rarely, 3 = sometimes, 5 = often). Psychometric properties have been previously reported [42], showing that the CRIES-13 is a valid measure of posttraumatic stress. In this study, the internal consistency of the CRIES-13 was 0.89. In this study, the CRIES-13 will be used to measure posttraumatic stress symptoms between each session during the course of treatment.

#### Outcome rating scale and session rating scale

To collect client feedback, we will use two brief questionnaires, the Outcome Rating Scale (ORS) and Session Rating Scale (SRS), which can be easily administered on a regular basis during treatment [43]. This allows treatment sessions to be evaluated at any time to ascertain whether individual treatments are ‘on the right track’ to a successful outcome. The ORS is primarily focused on the client’s well-being and is administered at the beginning of the treatment session. The SRS is administered at the end of the session and deals with how the client experienced the treatment session. The outcomes of the questionnaires are reflected in a graph per interview to allow the height of the score and progress to be visualized during the sessions.

### Sample size and power

This study implemented a non-inferiority trial. A non-inferiority trial is a type of clinical research study that aims to demonstrate that a (new) treatment is not worse than an existing treatment by a prespecified margin. Because the non-inferiority margin for CAPS-CA-5 scores had not yet been determined at the start of this study, we used the article published by Sloan et al. [44] to estimate the non-inferiority margin. The primary outcome was the total score on the Clinician-Administrated PTSD Scale for DSM-5 (CAPS-5). Non-inferiority was defined as a score of 10 points. However, the results showed that during follow-up, a non-inferiority margin of five points would have been sufficient to yield the same conclusion. Therefore, based on the article by Sloan et al. [44] and clinical reasoning, the largest clinically acceptable effect to declare non-inferiority is a change in the CAPS-CA-5 score of five points (d). Based on the study by Sloan and colleagues, the true mean difference (μ_B_-μ_A_) between the treatments is -1.82 (after 12 weeks). In a non-published pilot study of 17 adolescents, we calculated a mean total score on the CAPS-CA-5 of 38.2 with a standard deviation of 10.4 (σ). An equal number of participants will be included in both arms of the trial (r = 1).

For the estimation of the sample size (for 80 percent power and type 1 error of 2,5 percent) the following formula is used [45].$${n}_{A}=\frac{7.85{\sigma }^{2}\left(r+1\right)}{{\left(\left({\mu }_{B}-{\mu }_{A}\right)-d\right)}^{2}r}$$

According to this formula, 36,5 participants per arm are required. As in the previous sample size calculation, we used the baseline variables as covariates. Based on Borm et al. [46, 47] we estimate that the design factor will be equal to 0.75, because we assume a correlation of 0.5 between the two measurements. Hence, we would need 36.5*0.75 = 27.4 participants per group. To compensate for an unknown clustering effect and unknown psychometric properties, and given the need to compensate for an expected dropout rate, we plan to include 40% more participants (76 participants in total), so that 38 participants will be recruited per arm.

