Hence, the limited number of studies investigating the effectiveness of treatments for young individuals with Complex PTSD underscores the need for further research [10]. In their position paper published in 2019, the ISTSS deemed treatment recommendations premature because of current knowledge gaps. This indicates a pressing requirement for research exploring the effects of trauma-focused treatment on adolescents with (symptoms of complex) PTSD resulting from (repeated) sexual abuse, maltreatment, and/or domestic violence. To address this research gap, the present study describes an RCT aimed at investigating the differences in treatment effects between two treatment approaches (i.e., phase-based versus immediate trauma-focused) in adolescents with (symptoms of complex) PTSD resulting from a history of repeated sexual and/or physical abuse during childhood.

The primary objective of this study is to compare the results of phase-based treatment with those of immediate trauma-focused (i.e., eye movement desensitization and reprocessing; EMDR) therapy using a two-arm randomized controlled trial design. The first aim is to determine whether immediate trauma-focused treatment is not worse than phase-based treatment in reducing PTSD symptoms. If trauma-focused treatment is found to be equally effective when applied, it could lead to significant reductions in treatment duration. Second, we aim to investigate whether the phase-based therapy approach yields superior outcomes compared to the direct trauma-focused condition in terms of Complex PTSD symptoms, including emotion regulation, interpersonal problems, and self-esteem. Additionally, we will examine comorbid symptoms and dropout rates as secondary outcome measures. The third objective of the current study is to identify potential moderators and predictors of dropout or treatment responses/non-responses under both treatment conditions. We hypothesize that the presence of affect dysregulation and interpersonal problems at the beginning of therapy will be associated with poorer outcomes in the direct trauma-focused condition. Finally, we will examine the relationship between the reduction of posttraumatic stress symptoms in adolescents and a decrease in self-reported parental/caretaker stress. This objective addresses the clinical assumption that managing parental stress should be prioritized before initiating PTSD treatment in adolescents.

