### Statistical analysis

Data will be analyzed using SPSS V.29.0 for Windows (SPSS Incorporated). Pretreatment group differences with respect to age, sex, ethnicity, and type of traumatic event will be assessed using independent-sample t-tests for continuous data and χ^2^ tests for categorical data. Before testing, we will check all the data according to the appropriate assumptions.

To answer the primary question, a repeated-measures ANCOVA will be conducted. Baseline scores will be included as covariates, time as a categorical variable, and treatment condition as a fixed effect. The intercept will be treated as a random effect. We will examine the residuals to assess the model assumptions and goodness-of-fit. *P-values* will be reported to four decimal places, with *P-values* less than 0.001 reported as *p* < 0.001. For all tests, we will use 2-sided *P-values* with alpha =  < 0.05 level of significance. As this is a non-inferiority trial, both intention-to-treat and per-protocol analyses will be performed.

To evaluate the secondary outcomes, a repeated-measures ANCOVA will be conducted for the total score on the ECR-RC, DERS, RSES, RCADS, CPTCI, CBCL, OBVL, and Y-OQ-30. Baseline scores will be included as covariates, time as a categorical variable, and treatment condition as a fixed effect. The intercept will be treated as a random effect. We examine the residual to assess the model assumptions and goodness-of-fit. Delta-scores for pre- to post-treatment (T1 and T3) will be calculated, and an independent sample t-test will be used to compare the TRAP + EMDR and EMDR-only conditions. For the calculation of effect sizes (Cohen’s *d*) for within-group effects, we will divide the difference in means between pre- and post-treatment by the standard deviation of the difference in means. *P-values* will be reported to four decimal places, with *P-values* less than 0.001 reported as p < 0.001. For all tests, we will use 2-sided *P-values* with alpha =  < 0.05 level of significance.

To determine PTSD symptom changes on the CRIES-13, we will analyze the data for all time points in a linear mixed model. Time, treatment condition, the interaction term time × treatment condition, and sex will be entered as fixed factors, and age as a covariate in the model. The impact of missing data on outcome measurements will be evaluated using different methods, such as Last Observation Carry Forward (LOCF) and Multiple Imputation (MI).

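### The stated 80% power depends on an unsupported assumption that EMDR-only is truly 1.82 points better; if the treatments are equal, the protocol's own formula gives about 54% to 68%

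*Protocol article*

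**What the plan says.** The Background states the first aim as to "determine whether immediate trauma-focused treatment is not worse than phase-based treatment in reducing PTSD symptoms". It then gives the practical motive: "If trauma-focused treatment is found to be equally effective when applied, it could lead to significant reductions in treatment duration".

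The Sample size and power section sets the non-inferiority margin at 5 points on the CAPS-CA-5. On the basis of a published trial whose outcome was the CAPS-5, it takes the true mean difference "between the treatments is -1.82 (after 12 weeks"). For the spread, it reports a pilot study of 17 adolescents: "we calculated a mean total score on the CAPS-CA-5 of 38.2 with a standard deviation of 10.4". The calculation is made "for 80 percent power and type 1 error of 2,5 percent". The formula gives 36.5 per arm, and a design factor of 0.75 for baseline adjustment reduces this to 27.4. To cover clustering, psychometric properties and dropout together, "we plan to include 40% more participants (76 participants in total"), which is 38 per arm.

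The section gives power for this one value of the true difference only.

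**The concern.** In a non-inferiority design, power depends heavily on the true difference assumed. Assuming that the new treatment is somewhat better moves the planning point away from the margin and reduces the sample size. That is a legitimate choice if it is justified and presented as favourable. Here it is neither.

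- The article describes another trial's estimate as the true difference between the treatments. It does not say which treatments that trial compared or why its result should carry over.
- The Discussion says that, to the authors' knowledge, this is the first randomised trial of this comparison in this population. The value therefore cannot have been estimated for it.
- Under Study design, both arms receive 12 EMDR sessions and the phase-based arm receives 12 skills sessions first. The article offers no argument that leaving out the skills sessions would lower CAPS-CA scores further.
- The case for the shorter treatment in the Background needs only equality.

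At stake is whether the stated 80% describes the chance of success in the scenario the trial is meant to address.

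**Working it through.** **Inputs, all from the Sample size and power section:** margin d = 5; assumed difference Δ = -1.82; SD σ = 10.4; allocation ratio r = 1; one-sided alpha 2.5% and power 80% (constant 7.85); design factor 0.75 (1 - 0.5²). The Statistical analysis section says "For all tests, we will use 2-sided" P-values at 0.05, which matches a one-sided 2.5% for the non-inferiority bound.

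**Step 1: reproduce the plan's figure.**

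n = 7.85 × σ² × (r + 1) / ((Δ - d)² × r)

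= 7.85 × 108.16 × 2 / (-6.82)² = 1698.1 / 46.51 = 36.5 per arm

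36.5 × 0.75 = 27.4 per arm. Both stated figures reproduce.

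**Step 2: direction of the assumption.** The article does not say which arm is A and which is B, but the result settles it. The term 6.82 arises only if the new arm, EMDR-only, is assumed better. If it were 1.82 points worse, the denominator would be 3.18² = 10.11 and the formula would require 1698.1 / 10.11 = 167.9 per arm.

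**Step 3: requirement at zero difference.**

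1698.1 / 25 = 67.9; × 0.75 = 50.9 evaluable per arm. With the same 40% inflation this is 50.9 × 1.4, or about 71 recruited per arm, against 38 planned.

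**Step 4: power at the planned size.**

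Power = Φ( (5 - Δ) / (σ × √0.75 × √(2/n)) - 1.96 ), with σ × √0.75 = 9.007.

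- n = 27.4: standard error 9.007 × √(2/27.4) = 2.433. At Δ = 0: 5/2.433 - 1.96 = 0.095, power 53.8%. At Δ = -1.82: 6.82/2.433 - 1.96 = 0.843, power 80.0%.
- n = 38: standard error 9.007 × √(2/38) = 2.066. At Δ = 0: 5/2.066 - 1.96 = 0.460, power 67.7%. At Δ = -1.82: 6.82/2.066 - 1.96 = 1.341, power 91.0%.

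| Evaluable per arm | EMDR-only better by 1.82 | No difference |
|---|---|---|
| 27.4 (40% inflation used up) | 80% | 54% |
| 38 (no loss, no clustering) | 91% | 68% |

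Using the noncentral t distribution instead of the normal lowers the zero-difference figures by about one percentage point, to 52% and 67%.

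**Step 5: which row applies.** Going from 38 to 27.4 is a loss of 1 - 27.4/38 = 28%. The article gives no separate dropout rate, so the two rows bound the range. With 32 evaluable per arm, for example, power at zero difference is 60%.

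**The case against.** **Nothing is miscalculated, and the source is cited.** Both are true. A reader might infer an arithmetic error, but the formula is applied correctly. What is missing is a reason for using the value here and an acknowledgement that it is favourable.

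**54% is the low end.** It applies only if the whole 40% allowance is consumed. The result should be quoted as a range, 54% to 68%. Even the upper end is below 80%.

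**The planned analysis is not the single-measurement formula.** This is the strongest objection. The Statistical analysis section plans a repeated-measures ANCOVA and lists no treatment-by-time interaction. The CAPS-CA section schedules the measure at T3 and T4 in both arms. If the treatment effect is averaged over those visits, the variance factor becomes (1 + ρ)/2 - 0.25 instead of 0.75. The document does not give ρ, the correlation between T3 and T4. Assuming ρ of 0.5 to 0.7, the factor is 0.50 to 0.60, and power at zero difference is 63% to 71% with 27.4 per arm and 77% to 84% with 38. So the documents do not support saying flatly that the trial lacks 80% power at equality. But the protocol derives its own 80% from one follow-up measurement, and on that basis the comparison stands.

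**Aim 2 does not contradict the assumption.** A reader might set the second aim, superiority of the phase-based arm, against the -1.82. That aim concerns emotion regulation, interpersonal problems and self-esteem, not the CAPS-CA total, so it carries no weight here.

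**The SD is uncertain.** It rests on 17 adolescents, but the uncertainty runs in both directions. It is therefore held at 10.4 throughout and forms no part of the argument.

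**An article may leave sensitivity calculations to a fuller document.** This is fair as far as omissions go. The point here is a power figure that the article itself states, and the input on which it depends.

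**Conclusion.** The point stands as an unsupported input to the stated power, not as a calculation error. The 80% is conditional on EMDR-only being truly 1.82 points better. At equal effectiveness, the protocol's own SD, margin, alpha and design factor give about 54% to 68%, depending on how much of the 40% allowance is lost. The chance of failing to show non-inferiority between equal treatments would then be 32% to 46%, not 20%.

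These figures rest on the single-follow-up formula, an SD of 10.4 and a baseline correlation of 0.5, all as the protocol assumes. An effect averaged over T3 and T4 could bring power close to or above 80% if few participants are lost.

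A reader might go further and conclude that the sample size is invalid, or that a failed non-inferiority test would be misread as evidence against EMDR-only. The documents support neither. The planned analysis remains valid at 76 participants. Nothing in the text indicates such a misreading, and the Discussion itself warns that non-inferiority trials may not give definitive conclusions.

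**What to change.** Keep 76 participants and change the text of the Sample size and power section in two places.

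1. Describe -1.82 as a favourable planning assumption taken from a different trial on the CAPS-5 and not estimated for EMDR-only versus TRAP+EMDR. State which arm it favours.
2. Restate power along these lines: 80% if EMDR-only is truly 1.82 points better; about 54% (27.4 evaluable per arm) to 68% (38 per arm) if the treatments are equal, on the single-follow-up formula. Add that a treatment effect averaged over T3 and T4 could raise these figures, depending on the correlation between the two visits.

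The cost is a few sentences and a less favourable power statement. No extra participants are needed and the analysis does not change.

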### Data collection and management

Confidentiality is maintained throughout the current study. The handling of subjects’ personal data is in accordance with the European General Data Protection Regulation (in Dutch: Algemene Verordening Gegevensbescherming, AVG). To maintain anonymity of all data, participants will only be identifiable by a unique code assigned to the data of their inclusion. The code list will be digitally stored on the secured drive of Karakter, which is password protected and is only accessible to researchers involved in the project. Non-anonymous data (e.g., informed consent documents) will be digitalized and stored in password-secured folders that provide restricted access. All local databases will be secured with password-protected access systems. The online electronic data capture software CASTOR EDC will be used to collect and store the questionnaire data. All paper documents are stored in a locker at Karakter Child and Adolescent Psychiatry. Access to this storage is accessible to only a select few researchers.

### Statistical analysis

Data will be analyzed using SPSS V.29.0 for Windows (SPSS Incorporated). Pretreatment group differences with respect to age, sex, ethnicity, and type of traumatic event will be assessed using independent-sample t-tests for continuous data and χ^2^ tests for categorical data. Before testing, we will check all the data according to the appropriate assumptions.

To answer the primary question, a repeated-measures ANCOVA will be conducted. Baseline scores will be included as covariates, time as a categorical variable, and treatment condition as a fixed effect. The intercept will be treated as a random effect. We will examine the residuals to assess the model assumptions and goodness-of-fit. *P-values* will be reported to four decimal places, with *P-values* less than 0.001 reported as *p* < 0.001. For all tests, we will use 2-sided *P-values* with alpha =  < 0.05 level of significance. As this is a non-inferiority trial, both intention-to-treat and per-protocol analyses will be performed.

To evaluate the secondary outcomes, a repeated-measures ANCOVA will be conducted for the total score on the ECR-RC, DERS, RSES, RCADS, CPTCI, CBCL, OBVL, and Y-OQ-30. Baseline scores will be included as covariates, time as a categorical variable, and treatment condition as a fixed effect. The intercept will be treated as a random effect. We examine the residual to assess the model assumptions and goodness-of-fit. Delta-scores for pre- to post-treatment (T1 and T3) will be calculated, and an independent sample t-test will be used to compare the TRAP + EMDR and EMDR-only conditions. For the calculation of effect sizes (Cohen’s *d*) for within-group effects, we will divide the difference in means between pre- and post-treatment by the standard deviation of the difference in means. *P-values* will be reported to four decimal places, with *P-values* less than 0.001 reported as p < 0.001. For all tests, we will use 2-sided *P-values* with alpha =  < 0.05 level of significance.

To determine PTSD symptom changes on the CRIES-13, we will analyze the data for all time points in a linear mixed model. Time, treatment condition, the interaction term time × treatment condition, and sex will be entered as fixed factors, and age as a covariate in the model. The impact of missing data on outcome measurements will be evaluated using different methods, such as Last Observation Carry Forward (LOCF) and Multiple Imputation (MI).

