## Method

### Study design

This study entails a single-blind, randomized controlled trial with two arms: a phase-based treatment condition (TRAP followed by EMDR) and a trauma-focused treatment condition (EMDR only). In the TRAP-EMDR condition, participants receive 12 sessions of skills training (TRAP; the Dutch adolescents version of the STAIRS protocol), followed by 12 sessions of EMDR therapy. In the other condition, the participants receive 12 EMDR sessions. The two groups will be compared for several outcome variables before treatment, immediately after 12 sessions (post-treatment), and six months post-treatment (follow-up) (see Fig. 1). This study will be coordinated by the Karakter Academic Center for Child and Adolescent Psychiatry in the Netherlands. The study started in 2018, paused for seven months in 2020 due to COVID-19, and continued in September 2020. This study is ongoing and is expected to be completed by 2024.

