### Primary outcome

#### The clinician-administered ptsd scale for children and adolescents

The Clinician-Administered PTSD Scale for Children and Adolescents (CAPS-CA) [24] is a structured clinical interview used to establish the diagnostic status of the DSM-IV and DSM-V criteria for PTSD. The interviewer can rate the frequency and intensity of each symptom on a five-point Likert scale. Furthermore, each symptom can be rated as present or absent, as proposed by Weathers, Ruscio, and Keane [25] to score a symptom as being present. The CAPS-CA can be reliably administered by different interviewers. The Dutch CAPS-CA showed as good internal consistency, inter-rater reliability, convergent and divergent validity, and concurrent validity as the original English version [26]. The CAPS-CA will be administered three times (T1, T3, and T4) for adolescents in the EMDR-only group and four times in the TRAP + EMDR group (T1, T2, T3, and T4). Adding the CAPS-CA at T2 in the TRAP + EMDR condition will provide information about the effects and necessity of skills training TRAP as a standalone treatment.

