## Discussion

The present paper describes the rationale, study design, and methods of the MARS-study: an RCT evaluating the effects of a phase-based treatment model compared to purely trauma-focused therapy in young individuals diagnosed with PTSD and on the possible symptoms of complex PTSD resulting from (repeated) sexual and/or physical abuse during childhood.

This study had several strengths. First, it sought to assess the effectiveness and efficacy of two widely utilized treatment models in a group of patients who are often overlooked in research owing to their complex symptomatology. To the best of our knowledge, an efficacy study of adolescents who have experienced (repeated) sexual and/or physical abuse during childhood is unprecedented. Second, although a phase-based trauma-focused model has recently been studied in adults (15–17), no similar study has been conducted in adolescents. Research on the effectiveness of trauma treatment in adolescents (symptoms of complex) PTSD is limited [20]. To our knowledge, this is the first randomized controlled trial to investigate and compare the effects of regulation skill training with those of a direct trauma-focused treatment approach in this population. Third, adding a follow-up period allows us to track the long-term effects of both treatments, which can provide valuable information about the sustainability of the treatment effects and whether there are any delayed or long-term benefits (sleeper effects) or side effects. Therefore, we can make more reliable and comprehensive conclusions regarding the effectiveness of and differences between interventions. Additionally, by adding a mid-treatment measurement, it is possible to investigate the effects of TRAP and better assess the added value of this phase-based treatment approach.

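### The primary CAPS-CA model has no treatment-by-time term and no visit is named for the non-inferiority decision, so the listed model gives a pooled effect rather than the single-visit contrast that was sized

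*Protocol article*

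**What the plan says.** The first aim in the Background reads: "The first aim is to determine whether immediate trauma-focused treatment is not worse than phase-based treatment in reducing PTSD symptoms". It gives no time point. The Statistical analysis section then says: "To answer the primary question, a repeated-measures ANCOVA will be conducted". The listed terms are "Baseline scores will be included as covariates, time as a categorical variable, and treatment condition as a fixed effect", followed by "The intercept will be treated as a random effect". No interaction is listed.

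On timing, the CAPS-CA section says: "The CAPS-CA will be administered three times (T1, T3, and T4) for adolescents in the EMDR-only group and four times in the TRAP + EMDR group"; the additional assessment is T2, at mid-treatment. The Study design section compares the arms before treatment, post-treatment and at six months, without ranking them. The margin in Sample size and power (5 points) is not attached to a visit of this trial. That section sizes the trial from a between-treatment difference of -1.82, quoted at 12 weeks from the cited study, and from a design factor of 0.75 for a correlation of 0.5 between two measurements.

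The Discussion says follow-up will help to show "whether there are any delayed or long-term benefits (sleeper effects) or side effects".

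**The concern.** A non-inferiority conclusion is a claim about one defined difference set against one margin. Here the difference is left open. Without a treatment-by-time term the model assumes the same treatment difference at every visit it contains and estimates that common value. If the true difference changes between the end of treatment and six months, the coefficient describes neither visit. A deficit at one visit can be offset by parity or benefit at the other.

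Two other parts of the article pull against such an effect. The sample size treats the comparison as one baseline and one outcome. The Discussion wants follow-up to show delayed effects, which are changes in the treatment difference over time, and the listed primary model sets such changes to zero.

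**Working it through.** **1. The plan's sample size.** Inputs from Sample size and power: SD 10.4, difference -1.82, margin 5, ratio 1, constant 7.85 (80% power, 2.5% one-sided).

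- n = 7.85 × 10.4² × 2 / (-1.82 - 5)² = 36.5 per arm, as stated.
- Design factor 1 - 0.5² = 0.75, so 36.5 × 0.75 = 27.4 per arm, as stated.
- 27.4 × 1.4 = 38.3, stated as 38 per arm, 76 in total.

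The figures reproduce. The factor 1 - 0.5² applies to one outcome adjusted for one baseline, so the sized quantity is a single-visit contrast.

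**2. What the listed model estimates.** The article does not say which visits make up time. T1 is the covariate. T2 exists in one arm only and offers no between-arm comparison. That leaves T3 and T4. With both entered, complete data and no interaction, the treatment coefficient is (difference at T3 + difference at T4) / 2. With dropout it is a weighted average.

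**3. Precision of the two quantities.** Baseline-adjusted SD at one visit: 10.4 × √0.75 = 9.007. SD of the T3/T4 average: 9.007 × √((1 + ρ)/2), where ρ is the residual T3–T4 correlation. The article gives no value for ρ; 0.5 and 0.7 are assumed.

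- ρ = 0.5: 9.007 × √0.75 = 7.80
- ρ = 0.7: 9.007 × √0.85 = 8.30

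**4. Illustration.** Assume a true deficit for EMDR only of 5 points at T3 (exactly at the margin) and 0 at T4. The pooled effect is 2.5. The probability of declaring non-inferiority is Φ((5 - 2.5)/SE - 1.96), with SE = SD × √(2/n).

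| ρ | n per arm | SE | Pooled test passes | T3 contrast passes |
|---|---|---|---|---|
| 0.5 | 27.4 | 2.11 | 22% | 2.5% |
| 0.5 | 38 | 1.79 | 29% | 2.5% |
| 0.7 | 27.4 | 2.24 | 20% | 2.5% |
| 0.7 | 38 | 1.91 | 26% | 2.5% |

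With equal SDs at the two visits the same figures hold in reverse, if T4 is the target and the deficit is there.

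**5. Power of a single-visit contrast.** At 38 per arm SE = 9.007 × √(2/38) = 2.07. The distance from the assumed difference to the margin is 1.82 + 5 = 6.82. Power = Φ(6.82/2.07 - 1.96), about 91%, before dropout and clustering. For the pooled effect with the same constant difference it is Φ(6.82/1.79 - 1.96), about 97%, at ρ = 0.5, and Φ(6.82/1.91 - 1.96), about 95%, at ρ = 0.7.

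**The case against.** The strongest reply is that a common post-baseline effect is a legitimate estimand, and that the stated N is conservative for it. In the illustration the average deficit is 2.5, truly inside the margin, so a pass is the right answer for that estimand. It is an error only if one visit is the target. The pattern of 5 points and then 0 has no support in the documents, and even then the pooled test fails 71% to 80% of the time. All of this stands, and for that reason the figures are an illustration and not an error rate of the trial. It does not remove the problem, because the article never declares the pooled effect as its estimand and sizes the trial for something else.

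Several stronger readings are tempting and are not supported:

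- A reader might take the CRIES-13 model, where "Time, treatment condition, the interaction term time × treatment condition, and sex will be entered as fixed factors", as proof that a required term was dropped from the primary model. But no baseline covariate is listed for that model and it uses all time points, so it needs the interaction to express any treatment effect. The primary model conditions on baseline, and its main effect is already an adjusted group difference.
- A reader might extend the point to every secondary outcome. The article also plans a T1-to-T3 delta-score t-test for these, which is a visit-specific contrast. Table 1 as printed shows only one later assessment for the Y-OQ-30 and OBVL and a single assessment for the CBCL, although it has no T4 column and may not be complete.
- A reader might conclude that the trial cannot detect delayed effects at all. Only the listed model has that limit. The data will be collected, and a separate analysis plan may add visit contrasts.
- A reader might take T3 as the implied primary visit. The 12 weeks belong to the cited study, and the 5-point margin is argued from that study's follow-up results.

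A separate analysis plan could also add the interaction. The point does not rest on silence, however: the article states a term list, and that list yields a pooled effect.

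**Conclusion.** The point holds for the primary outcome. As listed, the primary model has no treatment-by-time term and the article names no visit for the 5-point decision. If T3 and T4 enter, the result is a pooled effect that differs from the sized single-visit contrast and cannot show a difference that changes between visits.

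The size depends on assumptions: one visit taken as the target, a true deficit of 5 there and 0 at the other, and residual correlation 0.5 to 0.7. Under these, non-inferiority is declared about 20% to 29% of the time instead of 2.5%. Which visits enter the model is an inference from the assessment schedule. The matter should be corrected before analysis; it is a defect of estimand and model, not of the sample-size arithmetic.

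**What to change.** For the primary model:

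- Add treatment × time.
- State that only the visits common to both arms, T3 and T4, enter it, and that the one-arm T2 does not.
- Prespecify one visit's treatment contrast as the non-inferiority test against the 5-point margin, with the other visit as secondary. T3 fits the post-treatment sizing best, but the choice is the sponsor's.
- If a pooled effect is really wanted, declare it as the estimand and say why an average over the two visits answers the question.

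For secondary scales with two post-baseline visits, add the same interaction; the delta-score t-test already gives them a T3 contrast.

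The cost is one model term and a sentence or two of text. N stays at 38 per arm. What is given up is the precision from averaging: under the assumed correlations the pooled standard error is √0.75 = 0.87 to √0.85 = 0.92 of the single-visit one, and power at 38 per arm is about 91% instead of 95% to 97%, before dropout and clustering.
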